### Intervention description {11a}

The intervention is a 3-week internet-based self-help program with guidance on demand called ROCO. The self-help program consists of 6 thematic modules including texts, videos, graphics, exercises, and for each module a weekly task. The 6 thematic modules are supplemented by an introduction and a conclusion. For a detailed description, see Table 1. Furthermore, the self-help program comprises a page with information on what to do in an acute crisis, including a list with emergency contacts, as well as a page named *Toolbox,* where the weekly tasks are listed. Participants also can track their symptoms on a page named *Mood-Tracker*.

**Table 1 Tab1:** Outline of the content of the internet-based self-help program ROCO

Introduction	Information about the self-help program
1. Identifying consequences and challenges	Information about psychological distress/adjustment problems due to the COVID-19 pandemic, assessment of the current state (bodily sensations, positive and negative feelings), resource-oriented weekly task
2. Understanding own feelings	Information about feelings such as anxiety, helplessness, anger, sense of shame and sadness, strategies to cope with these feelings, acceptance-oriented weekly task
3. Changing the perspective	Information about the influence of thoughts, automatic thoughts, rumination and irrational beliefs, exercises to challenge own thinking patterns, weekly task on rumination
4. Strengthening resilience	Information about resilience and three possible ways of gaining resilience, namely coping, joie de vivre and optimism, exercises to promote these, resource-oriented weekly task
5. Finding rest	Information about sleep, sleep hygiene and relaxation techniques, progressive muscle relaxation as a weekly task
6. Taking care of oneself	Information about the concept of posttraumatic growth and the importance of pleasure, exercises of gratitude and mindfulness, resource-oriented weekly task
Conclusion	Information about the importance of practicing and transferring what has been learnt to daily life

Participants are encouraged to work through two of the 6 thematic modules per week. One module takes between 40 to 80 min to complete. However, participants can determine the timing and order of the modules themselves. The first module includes information about possible psychological consequences and challenges concerning the situation surrounding COVID-19. In the second module, participants receive information concerning ways to deal with difficult feelings that may arise due to the current situation. The third module focuses on restructuring thought patterns and cognitive thinking traps and the fourth module on promoting resilience and coping skills. The fifth module consists of information about sleep hygiene and relaxation techniques. Finally, the last module addresses self-care and personal growth.

As the self-help program offers guidance on demand, participants have the possibility to contact a psychologist, but there is no scheduled contact per se. Participants can require guidance via chat function in the self-help program. They are informed that a psychologist will answer their request within 3 working days. Otherwise, the self-help program is unguided.

### Criteria for discontinuing or modifying allocated interventions {11b}

Since internet-based self-help is not suited as a treatment for acute suicidality, participants reporting an acute crisis during treatment are referred to an appropriate treatment. This will be recorded and reported as an adverse event.

### Strategies to improve adherence to interventions {11c}

Participants have the possibility to enable reminders within the self-help program. They can choose whether the reminder is sent via e-mail or text message after a certain time of inactivity. In the reminder, participants are encouraged to log into the self-help program again. We have further adopted a guidance on demand approach, since some form of support appears to increase adherence [19].

### Relevant concomitant care permitted or prohibited during the trial {11d}

Participants receiving the intervention, as well as participants in the waiting control condition are allowed to start any concomitant treatment at any time during the trial. However, participants must indicate at each measurement time whether they use concomitant psychological or psychiatric treatment (e.g., psychotherapy or drug therapy).

### Provisions for post-trial care {30}

The University of Bern will provide insurance for any harm suffered as a result from this trial.

### Outcomes {12}

All assessments are carried out online via self-observation questionnaires. The baseline measurement is at *t*_*0*_, the post-measurement *t*_*1*_ is at 3 weeks, the first follow-up measurement *t*_*2*_ is at 6 weeks, and the second follow-up measurement *t*_3_ is at 18 weeks after the baseline. Validated German versions of the questionnaires are used. For an overview of all outcome measures and corresponding measurement time points, see Fig. 2.

#### Primary outcome measure

##### Patient Health Questionnaire (PHQ-9)

The primary outcome measure is the score of the PHQ-9 [27]. The PHQ-9 is a 9-item measure assessing the severity of depressive symptoms. All 9 DSM-IV criteria for depression are scored on a scale from 0 = not at all to 5 = nearly every day. A score of 5 represents a mild depression, a score of 10 a moderate depression, a score of 15 a moderately severe depression, and a score of 20 a severe depression [29]. The PHQ-9 showed good internal consistency (Cronbach’s alpha between 0.86 and 0.89) [30, 31].

#### Secondary outcome measures

##### Depression Anxiety Stress Scale (DASS-21)

The DASS-21 is a short-form of the DASS and is used to assess depressive mood, anxiety, and chronic stress during the past week [32]. The DASS-21 consists of 21 items which are answered on a scale from 0 = did not apply to me at all to 3 = applied to me very much or most of the time. The internal consistencies of the scores for depressive mood, for anxiety, and for chronic stress (Cronbach’s alpha = 0.88, 0.76 and 0.86) lie between satisfactory and good [33].

##### Suicide Behavior Questionnaire Revised (SBQ-R)

The SBQ-R assesses suicidal experiences and behavior [28]. The SBQ-R consists of 4 items which are not scaled equally. A total score of the 4 items is calculated. The total score can range from 3 to 18 whereas a score greater than or equal to 8 is considered the most useful cutoff score for suicide risk in a clinical sample [28]. This SBQ-R cutoff is also used as an indication for suicidal tendencies (safety outcome). The internal consistency of the SBQ-R is satisfactory (Cronbach’s alpha = 0.72) [34].

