**Methods:**

The design is a parallel group randomized controlled trial. Participants are allocated to a 3-week self-help intervention plus care as usual or a 3-week waiting period with only care as usual. There are follow-ups after 6 weeks and 18 weeks. At least 80 participants with COVID-19 pandemic related psychological distress will be recruited. Primary outcome are depressive symptoms. Secondary outcomes include anxiety and chronic stress, suicidal experiences and behavior, health-related quality of life, generalized optimism and pessimism, embitterment, optimistic self-beliefs, emotion regulation skills, loneliness, resilience, and the satisfaction with and usability of the self-help program.

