### Eligibility criteria {10}

All interested persons must provide full written informed consent and are required to complete a baseline-screening questionnaire prior to randomization to assess eligibility.

Inclusion criteria are:
To be at least 18 years oldTo exceed a cutoff value of 4 points on the brief Patient Health Questionnaire (PHQ-9) [27]To be able to specify an emergency address in the event of an acute crisisTo have access to the internetTo understand and master the German language to the degree that one understands the content and instructions of the study

Exclusion criteria are:
The presence of suicidal tendencies (score ≥ 8 on the Suicide Behavior Questionnaire Revised (SBQ-R) [28]A known diagnosis of a psychotic or bipolar disorder

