## Statistical methods

### Statistical methods for primary and secondary outcomes {20a}

We will use linear mixed models with time (pre versus post-intervention measures) as a within-group-factor and study condition (immediate access versus control condition) as a between-group-factor to evaluate the efficacy of the internet-based self-help intervention. This primary analysis will be performed using the data from the baseline and the 3-week post assessment. To analyze the stability of the short-term effects of the internet-based self-help intervention, we will conduct within-group analyses using repeated measures ANOVA (pre-intervention, post-intervention and follow-up measures) and paired *t* tests when comparing only two time points.

Moreover, we will exploratory analyze possible predictors, mediators, and moderators for the relationship between the internet-based self-help program and the outcomes. The significance level is set at 5%. Analyses will be conducted using SPSS and R.

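### Within-group tests of the SBQ-R start from a baseline that the entry rule cuts to 3-7, so they can show a rise from regression to the mean alone

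*Protocol article*

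**What the plan says.** - **Entry rule** (Eligibility criteria {10}). Candidates "are required to complete a baseline-screening questionnaire prior to randomization to assess eligibility". One exclusion criterion is "The presence of suicidal tendencies (score ≥ 8 on the Suicide Behavior Questionnaire Revised (SBQ-R". Concealment mechanism {16b} places allocation after the baseline assessment is complete.
- **Role of the scale.** The abstract states: "Secondary outcomes include anxiety and chronic stress, suicidal experiences and behavior". The SBQ-R section stands under the secondary outcome measures and says "The total score can range from 3 to 18". Of the cutoff of 8 it adds: "This SBQ-R cutoff is also used as an indication for suicidal tendencies (safety outcome".
- **Analysis** (Statistical methods {20a}, headed as covering primary and secondary outcomes). Efficacy at 3 weeks is tested by a linear mixed model with time and "study condition (immediate access versus control condition) as a between-group-factor". For the stability of effects, "we will conduct within-group analyses using repeated measures ANOVA (pre-intervention, post-intervention and follow-up measures", with paired t tests where only two time points are compared. No exception is made for the SBQ-R.
- **Follow-up** (Trial design {8}). At 6 and 18 weeks both arms have had the program, so the arms are no longer compared and follow-up is read within groups.

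**The concern.** One score serves as the entry filter, as the starting value of an outcome and, through the same cutoff, as a safety indicator. People are kept because their score was low on one occasion. Unless the score is perfectly stable, some of them scored low by chance and will score higher next time, whatever the program does. A test of change from that first score includes this drift.

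The drift is in the adverse direction and the subject is suicidality. A program with no effect could show a within-group increase and a number of newly positive participants. At 6 and 18 weeks no randomised comparator remains to show that the increase came from selection. The article does not mention the effect.

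**Working it through.** **1. What follows from the text alone**

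- Scale 3-18, and 8 or more excluded, so the entry range is 3-7: 5 of 16 possible values.
- Share at 8 or more at t0 is 0% in both arms. It can only stay at zero or rise.

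Fig. 2, which holds the assessment schedule, is not shown. That the screening score is also the t0 outcome value is therefore inferred from Eligibility criteria {10} and Concealment mechanism {16b}.

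**2. Inputs for the size**

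The plan states no SBQ-R mean, SD, retest correlation or expected change, so there is no SBQ-R figure to reproduce. The one reliability figure is internal consistency: "The internal consistency of the SBQ-R is satisfactory (Cronbach’s alpha = 0.72". That is not a retest correlation. Assumed here: latent normal score, unselected mean μ = 5 or 6, SD 2.5, retest correlation r from 0.4 to 1.0, no treatment effect and no true change. From Sample size {14} and the 1:1 allocation: 80 in total, so 40 per arm.

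**3. Formula**

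With the cut at 7.5 and z = (7.5 − μ)/2.5, selection lowers the baseline mean by 2.5·φ(z)/Φ(z). The expected rise at the next assessment is that shortfall times (1 − r).

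- μ = 5: z = 1.0; shortfall 2.5 × 0.2420/0.8413 = 0.72. Rise at r = 0.4: 0.72 × 0.6 = 0.43. At r = 0.8: 0.72 × 0.2 = 0.14.
- μ = 6: z = 0.6; shortfall 2.5 × 0.3332/0.7257 = 1.15. Rise at r = 0.4: 1.15 × 0.6 = 0.69. At r = 0.8: 1.15 × 0.2 = 0.23.

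**4. Simulation with scores rounded and limited to 3-18**

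The last column is the proportion of paired t tests (n = 40) declaring a significant rise, against 2.5% nominal in that direction.

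| μ | r | Mean rise | Share at 8 or more | False rise |
|---|---|---|---|---|
| 5 | 0.4 | 0.43 | 12-13% | 23% |
| 5 | 0.8 | 0.15 | 7% | 10% |
| 5 | 0.95 | 0.05 | 4% | 6% |
| 6 | 0.4 | 0.69 | 21% | 48% |
| 6 | 0.8 | 0.25 | 12% | 19% |
| 6 | 0.95 | 0.07 | 6% | 8% |
| either | 1.0 | 0 | 0% | none |

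**5. The opposing entry rule**

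Eligibility also requires a PHQ-9 above 4, which selects towards higher distress. A separate simulation added this filter (assumed PHQ-9 mean 9, SD 5, correlation 0.5 with the SBQ-R). With SBQ-R mean 5, SD 2.5 and r = 0.6, the rise fell from 0.29 to 0.22 points. The filter weakened the rise and did not reverse it.

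**6. The randomised comparison**

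Let δ be the true effect and b the drift from selection. Expected change is δ + b in the intervention arm and b in the waiting arm. The difference is (δ + b) − b = δ. In simulation with no effect, the between-arm test of change (40 per arm) rejected in about 5% of trials, which is the nominal rate.

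**The case against.** Much of the opposing case stands.

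- **The efficacy test is sound.** A reader might infer that every pre-post analysis of the SBQ-R is uninterpretable. The documents do not support that: the 3-week analysis compares randomised arms that were truncated alike, and the drift cancels.
- **The rise is not certain.** A reader might infer that scores will rise. They can rise; by how much depends on quantities that the documents do not give. At r of 0.90-0.95 the rise is only 0.05-0.13 points, and at perfect stability it is zero. Real recovery could offset it.
- **Using one cutoff to exclude and to monitor is not an error.** Starting from 0% makes the 3-week count one of new cases, which can be compared between arms. The article nowhere says that a within-group rise will be reported as harm; the within-group tests are there to assess whether gains last.
- **Harm assessment does not rest on this score alone.** A reader might take the SBQ-R indicator as the trial's only safety information. Criteria for discontinuing {11b} and Adverse event reporting {22} also record acute crises, acute suicidality and hospitalization.
- **Little room to improve is partly the scale's doing.** The largest possible fall is 7 − 3 = 4 points. Under the same assumptions, though, average room above the floor of 3 is already only 2.3-3.1 points without selection, and 1.6-2.0 with it. This does not carry the point.

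It can also be said that outcome-specific handling belongs in an analysis plan that is not shown. That is fair for the choice of interval or covariates. It does not remove the point, because the article itself fixes both the entry rule and the within-group tests from the pre score, and for this outcome the two work against each other.

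**Conclusion.** The point holds for within-group results only. Change in the SBQ-R from t0, and the share at 8 or more compared with t0, are biased upward by the entry rule unless the score is perfectly stable. With an assumed unselected mean of 5-6, SD 2.5 and retest correlation 0.4-0.95, the bias is about 0.05-0.7 points, with 4-21% at 8 or more and no true change. A paired t test on 40 people would then declare a rise in roughly 6-48% of trials; the upper end needs both the higher mean and the lowest correlation.

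This matters most at 6 and 18 weeks, where no randomised comparison is available. The 3-week time-by-condition comparison and the primary outcome are unaffected. The conclusion assumes that the screening score serves as the t0 value, which the text suggests but the missing figure would have to confirm.

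**What to change.** In the SBQ-R section and Statistical methods {20a}:

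1. Keep the SBQ-R in the randomised 3-week comparison: baseline-adjusted difference in means, and the number at 8 or more by arm with a risk difference and confidence interval.
2. Take the SBQ-R out of the within-group ANOVA and paired t tests that use the t0 score.
3. Report the 6- and 18-week SBQ-R descriptively or relative to t1.
4. State that a rise from t0 is partly expected from the entry rule.

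The entry rule itself need not change. The cost is wording only, with no new data. The downside is that this one secondary outcome loses its formal within-group test from t0.

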##### 12-Item Short-Form Health Survey (SF-12)

The SF-12 assesses health-related quality of life and is the short version of the Medical Outcomes Study 36-Item Short-Form Health Survey [35]. The SF-12 consists of 12 items with varying answer format. There are two versions of the SF-12, one assessing the health-related quality of life over the past week and one assessing it over the past 4 weeks. In this study, the latter is used. From the 12 items of the SF-12, a Physical Component Score and a Mental Component Score can be calculated. The internal consistency of the subscales exceeds the recommended Cronbach’s alpha level of 0.70 [36] .

##### Life Orientation Test Revised (LOT-R)

The LOT-R is a 10-item scale assessing generalized optimism and pessimism [37]. The items are answered on a scale from 0 = strongly disagree to 4 = strongly agree. Three items form the score for pessimism and 3 items the score for optimism, whereas 4 items are unscored as they are filler items. The internal consistency is satisfactory with a Cronbach’s alpha of 0.69 for optimism and 0.68 for pessimism [38].

##### Bern Embitterment Inventory (BEI)

The BEI is an 18-item questionnaire assessing embitterment, whereby embitterment can be understood as the feeling of being disadvantaged by others and fate [39, 40]. The items are answered on a scale from 0 = I do not agree to 4 = I agree. The internal consistency for the total embitterment score is good (Cronbach’s alpha 0.89) [39]. In this study, the 6-item short version of the BEI is used [41].

##### General Self-Efficacy Scale (GSE)

The GSE is a 10-item questionnaire assessing optimistic self-beliefs [42]. The items are answered on a scale from 1 = not at all true to 4 = exactly true. The internal consistency (Cronbach’s alpha) for the total score ranges between .76 and .90 [42].

##### Self-report measure for the assessment of emotion regulation skills (SEK-27)

The SEK-27 assesses adaptive ways of coping with negative emotions [43]. The 27 items are answered on a scale from 0 = never to 4 = (almost) always. Two versions of the SEK-27 are available: a trait version assessing the coping with negative emotions in general and a prolonged state version assessing the coping with negative emotions over the last week. In this study, the latter is used. A total scale as well as the subscales attention, bodily awareness, clarity, understanding, regulation, acceptance, resilience, self-support, and goal-oriented readiness for confrontation can be formed. The total scale of the prolonged state version has an excellent internal consistency (Cronbach’s alpha = 0.90). The internal consistency of the subscales of the prolonged state version ranges from 0.72 to 0.81 [44].

##### UCLA Loneliness Scale (ULS)

The ULS is a measure assessing one’s subjective feeling of loneliness [45]. The items are answered on a scale from 1 = never to 4 = often. The original version of the ULS consists of 20 items and has an internal consistency (Cronbach’s alpha) ranging from 0.82 to 0.92 [45]. In this study, a 9-item version of the ULS is used.

##### Connor-Davidson Resilience Scale (CD-RISC)

The CD-RISC assesses resilience [46]. Items are answered on a scale from 0 = not true at all to 4 = true nearly all of the time. In this study, the 10-item version of the CD-RISC is used. The 10-item version has a good internal consistency (Cronbach’s alpha) of 0.84 [47].

##### Client Satisfaction Questionnaire-8 (CSQ-8)

The CSQ-8 assesses the satisfaction of the participants with the intervention [48]. The CSQ-8 consists of 8 items which are answered on a scale from 1 = poor to 4 = excellent. Since the CSQ-8 measures the satisfaction with the intervention, it can only be used after the intervention phase. THE CSQ-8 has an excellent internal consistency (Cronbach’s alpha) ranging from 0.87 to 0.93 [49].

##### System Usability Scale (SUS)

The SUS is used to assess the usability of a system such as mobile devices, websites and applications [50]. The 10 items of the SUS are answered on a scale from 1 = strongly disagree to 5 = strongly agree. A score between 0 and 100 can be calculated, indicating the usability of a system, in this case the internet-based self-help program. Since the SUS measures the system usability of the internet-based self-help program, it can only be used after the intervention phase. The English version of the SUS has an excellent internal consistency (Cronbach’s alpha) ranging from = 0.91 to 0.92 [51, 52].

#### Predictors and moderators

##### Demographic variables

Demographic variables include sex, age, country of residence, civil status, housing situation, current childcare situation, education, employment situation (before and during COVID-19 pandemic), income (before and during COVID-19 pandemic), current everyday working life, psychiatric medical history, concomitant psychological/psychiatric treatment, and COVID-19-specific questions (e.g., belonging to a risk group, own illness or instances of deceased family members due to the pandemic).

##### Adherence

The intensity and frequency of use of the self-help program is measured by indicators collected within the self-help program such as percentage of accessed pages or number of logins.

### Participant timeline {13}

(Figure 2).

**Fig. 2 Fig2:**
[figure not shown]
SPIRIT figure, schedule of enrolment, interventions, and assessments

### Sample size {14}

To specify the sample size needed for the different analyses, we conducted a power analysis based on a probability level of 0.05 and a power of 0.80 with G*Power [53] for a repeated-measures ANOVA with a within-between-interaction. To test the efficacy of the self-help program compared to the control condition, we expected a small-to-medium between group effect size of *d* = 0.35 and a correlation between the factors of at least *r* = 0.4. The expected effect size is based on the results of meta-analyses on the effectiveness of unguided internet-based self-help programs targeting depressive symptoms [17, 54]. We decided to base the expected effect size on unguided internet-based self-help programs as it is yet to be determined if a guidance on demand approach yields higher effect sizes than unguided self-help [23, 24] . Power analysis indicated a necessary sample size of 80 individuals. In consideration of a possible attrition rate between 5.4 and 45.5% at post-assessment, we aim to recruit between 80 and 120 participants at baseline [17].

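### The sample size of 80 matches an interaction effect twice the stated one; for d = 0.35 at r = 0.4, 80 participants give about 29% power, not 80%

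*Protocol article*

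**What the plan says.** Protocol article, Sample size {14}: the authors ran "a power analysis based on a probability level of 0.05 and a power of 0.80 with G*Power", "for a repeated-measures ANOVA with a within-between-interaction". The effect is given as "we expected a small-to-medium between group effect size of *d* = 0.35", with "a correlation between the factors of at least *r* = 0.4". On its origin the section says: "The expected effect size is based on the results of meta-analyses on the effectiveness of unguided internet-based self-help programs targeting depressive symptoms". The result is: "Power analysis indicated a necessary sample size of 80 individuals". Recruitment is set at 80 to 120 to allow for attrition of 5.4% to 45.5% at post-assessment. The f entered in G*Power is not printed.

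Statistical methods for primary and secondary outcomes {20a}: the efficacy analysis uses "linear mixed models with time (pre versus post-intervention measures) as a within-group-factor" and study condition as the between-group factor. "This primary analysis will be performed using the data from the baseline and the 3-week post assessment". The primary test is therefore a two-group, two-time-point interaction, the same structure as the sample size calculation. Trial design {8} gives 1:1 allocation and places the superiority claim at the 3-week assessment.

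**The concern.** A standardised difference of 0.35 between two groups is a small-to-medium effect, and 40 per arm is a small trial. With a pre-post correlation of only 0.4, the baseline measurement adds no precision to a change-score comparison: the change score has variance 2(1 − 0.4) = 1.2 against 1 for the post score alone. It is therefore implausible that 80 people give 80% power.

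The likely source is the step from d to f. In G*Power the interaction f is the standard deviation of the interaction cell effects divided by the within-cell SD, which is not the f of a two-group comparison of means.

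This test carries the trial's superiority claim. If true power is near 30%, a non-significant result is the more likely outcome even when the programme works as expected. A reader relying on the stated 80% could take such a result as evidence against a small-to-medium effect. A significant result would tend to overestimate the effect, as happens on average with underpowered tests.

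**Working it through.** **Inputs** (Sample size {14} unless noted): d = 0.35; r = 0.4; alpha = 0.05; power 0.80; interaction test with k = 2 groups. The number of measurements, m = 2, comes from Statistical methods {20a}, and 1:1 allocation from Trial design {8}.

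**1. Reproducing 80.** For the within-between interaction G*Power uses a noncentral F with λ = f²·N·m/(1 − r) and df = (1, N − 2).

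- f = d/2 = 0.175, N = 80: λ = 0.175² × 80 × 2/0.6 = 8.17; power 0.806.
- Same f, N = 78: power 0.796.

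The smallest even N is 80, an exact match. Other plausible entries do not give 80:

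| Entry | N for 80% power |
|---|---|
| f = 0.35, m = 2 | 22 |
| f = 0.175, m = 3 | 66 |
| f = 0.175, m = 4 | 56 |
| f = 0.175, λ = f²·N (option without r) | 260 |
| f = 0.175, between-factors test | 182 |
| f = 0.0875, m = 2 | 310 |

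**2. The f that corresponds to d = 0.35.** Take SD 1, equal baselines and a difference of 0.35 at 3 weeks. The cell means are (0, 0) for control and (0, −0.35) for intervention. Removing the row and column means leaves interaction effects of ±0.35/4 = ±0.0875 in all four cells, so f = 0.0875. Conversely, f = 0.175 corresponds to 4 × 0.175 = 0.70 SD, twice the stated effect.

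**3. Power for the stated effect.**

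- N = 80: λ = 0.0875² × 80 × 2/0.6 = 2.04; power 0.292.
- N = 120: λ = 3.06; power 0.411.
- Smallest even N for 80% power: 310.

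**4. Check without f.** The SD of the change is √(2(1 − 0.4)) = 1.095, so the standardised difference in change is 0.35/1.095 = 0.3195. A two-sample t test with 40 per arm has noncentrality 0.3195 × √20 = 1.43 and power 0.292, and again needs N = 310. A simulation of 200,000 trials with 40 per arm gave 0.293.

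**5. Other analyses, d = 0.35, r = 0.4.** The residual SD is 1 for the post score alone and √(1 − 0.4²) = 0.917 with baseline adjustment.

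| Analysis | Power, 80 analysed | Power, 120 analysed | N for 80% | Detectable d at 80 / 120 |
|---|---|---|---|---|
| Time-by-group interaction | 29% | 41% | 310 | 0.70 / 0.57 |
| Post score only | 34% | 48% | 260 | 0.63 / 0.52 |
| Baseline-adjusted | 39% | 55% | 218 | 0.58 / 0.47 |

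If 120 are recruited and 45.5% are lost, 120 × 0.545 ≈ 65 complete, and interaction power on completers is about 25%.

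**6. Sensitivity to r** (interaction test, d = 0.35).

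| r | 0.4 | 0.5 | 0.6 | 0.7 | 0.8 | 0.85 |
|---|---|---|---|---|---|---|
| Power, 80 analysed | 29% | 34% | 41% | 51% | 69% | 81% |
| Power, 120 analysed | 41% | 48% | 57% | 69% | 85% | 94% |

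**The case against.** Four points can be made for the plan.

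- **The f entered is not printed.** The d/2 explanation is therefore an inference. That stands, although the match is exact and none of the alternatives tried gives 80. The conclusion does not need it, because the change-score calculation uses only the printed d, r, alpha and N.
- **The correlation is given as a minimum, so 29% is a floor.** This also stands. With 80 analysed, however, power reaches 80% only near r = 0.85, more than double the planning value. With 120 analysed, r = 0.8 would be enough (85%), but the article makes no such assumption and expects attrition.
- **The mixed model might constrain the baseline means to be equal.** An article can leave that detail to a fuller plan. It would raise power at r = 0.4 to 39% with 80 analysed and 55% with 120, so the fair range at 80 is 29% to 39%.
- **The d of 0.35 might be scaled by the SD of change.** The article calls it a between-group effect taken from meta-analyses. Even on that reading, power with 80 is 34%.

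It is also true that the error biases neither the estimate nor the type I error, and that the article nowhere says a null result would exclude d = 0.35. These points limit the consequences but do not make the stated power correct.

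**Conclusion.** The concern holds. The printed inputs do not lead to 80. At d = 0.35, r = 0.4 and two-sided alpha 0.05, 80 analysed participants give 29% power for the named interaction test, or 39% with baseline adjustment. The required total is 310 or 218 respectively. The trial as sized has 80% power for a difference of about 0.70 SD, or 0.58 SD with baseline adjustment.

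These figures assume equal expected baselines, equal variances at both time points, 1:1 allocation, and d standardised by the SD at a single time point. The misstatement concerns the basis of the trial's size for its primary hypothesis and is too large to be put down to rounding or choice of software option. It must be corrected.

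**What to change.** Revise Sample size {14} as follows.

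- State that a 3-week difference of d = 0.35 with equal baselines corresponds to an interaction f of 0.0875.
- Replace the claim of 80% power with the power available at r = 0.4: about 29% for 80 analysed and 41% for 120 (39% and 55% if the primary model adjusts for baseline).
- Give the effects detectable with 80% power: about 0.70 SD for 80 analysed and 0.57 SD for 120 (0.58 and 0.47 with adjustment).
- Show how these change for r above 0.4, since 0.4 is given as a minimum.
- Preferably add that a non-significant result does not exclude d = 0.35 and that interpretation will rest on the estimate and its 95% confidence interval. The error itself does not compel this sentence, but it guards against misreading.

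The cost is rewording and a less favourable power statement. No extra participants are asked for. Trial status reports 99 recruited in January 2021, with recruitment due to end about April 2021, so on that timetable the text can be corrected before recruitment closes.
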